### Randomization and allocation

Once eligibility is confirmed and consent is obtained, the participants will be randomized into the study arms/groups using non-stratified permuted blocks of varying lengths (*n* = 6 blocks; patient distribution = 1:1:1). Randomization will be conducted using an internet-based randomization system. Once a patient has consented to participate in the trial, the designated staff will log in into the randomization system web page to confirm eligibility; a random allocation will be sent to the pharmacy.

A responsible unit unrelated to this clinical trial will be designated to complete the packaging and distribution of the drugs (test drugs and control drugs) under the supervision of the statistician. Allocation concealment will be ensured. The randomization codes will be distributed through a data network platform designed by the Data Management Center of Jiangsu Famaisheng Medical Technology. Afterwards, participants will be randomly assigned to different treatment groups.

### Treatment cycles

The treatment is planned for 5 days in one cycle. All interventions will be stopped after the 5-day treatment period and 1-week of follow-up.

The pain associated with acute GA is self-limiting; that is, it can resolve on its own after approximately 1 week without medication. The participants will be informed on the consent form that if they cannot bear the pain, they can withdraw from the study at any time and choose other treatment options.

### Test drugs and blinding

The study drug and its placebo are provided by China Resources Sanjiu Medical & Pharmaceutical Co., Ltd. Etoricoxib will be purchased from Merck and Co., Inc. The placebo of etoricoxib was manufactured by Nanjing Hengzheng Pharmaceutical Research Institute Co., Ltd., which is responsible for all processes of placebo production and production processing from ingredients to aluminum molding.

All trial investigators will be blinded to the interventions. Pharmacy staff will maintain a record of the treatments administered. All trial participants, care providers, and outcome assessors will be blinded to treatment. Each treatment has an equivalent placebo to ensure that blinding is maintained throughout the study.

All investigators involved in the trial will be blinded to treatment. Patients will not be informed of their assigned treatment during the study. Pharmacy staff will keep a record of allocated treatment arms in the event of emergency unblinding.

The treatment code for a participant can be broken by any clinician, either directly or via contact with the principal investigator. Allocation lists will be made available to the site that will be provided 24-h cover by the pharmacy. Thus, the central pharmacy can access the allocation list. Where possible, the local investigator should aim to discuss the need for unblinding with the coordinating investigator, and attempts to preserve blinding of relevant research staff (data collection, analysis, and interpretation) will be made. The coordinating investigator is responsible for pharmacovigilance management and reporting.

### Measurements

Demographic data such as age, sex, ethnicity, race, and body mass index will be recorded. Individuals will receive the following instructions during the trial period: no alcohol, low-purine, low-fat diet, and plenty of water (≥ 2000 ml/day); avoid predisposing factors such as joint cold, trauma, and excessive fatigue; and avoid use of diuretics, salicylic acid preparations, glucocorticoids, and other drugs that affect uric acid metabolism and excretion. Before the beginning of treatment and after 5 days of treatment, medical histories will be recorded for each patient, and laboratory examinations will be performed and will include the following: C-reactive protein, interleukin, blood routine, blood biochemistry, routine urine test, and electrocardiogram. In addition, the tenderness, redness, and swelling of the involved joint, symptom relief time, patient satisfaction, and 36-Item Short Form Survey values will also be collected. The study team will build and maintain electronic case report form data and ensure data completeness and quality periodically by means of internal audits. Double data entry will be used to ensure data quality. All efforts will be made to maintain confidentiality of patient data by using multiple means, such as de-identification, use of password-protected secure servers, and restriction of access to study team members.

### Drug combination

In this study, all drugs will be considered as combined drugs. Details including trade name, dosage, indications, and duration of medication will be recorded in the case report form. Whether a participant should withdraw from the trial because of the nature of the combined drugs will be judged by the study investigators. The use of diuretics, salicylic acid preparations, glucocorticoids, and other drugs that affect uric acid metabolism and excretion will be avoided.

### Statistical analysis

The statistical analysis plan was developed by professional statisticians upon consultation with the main trial investigators. The data will be stored at the data management center of Jiangsu Famaisheng Medical Technology Co., Ltd., and processed by in-house statisticians blinded to group allocation. The analyses will be conducted using SAS version 9.2 (SAS Institute Inc., Cary, NC, USA) and will cover the number of participants enrolled in each group, the number of patients who dropped out of the study and the reason for the dropout, demographic and other baseline characteristics, compliance, efficacy analysis, and safety analysis.

Descriptive and comparative analyses will be performed. Qualitative data will be described using frequency tables, percentages, or constituent ratios and compared using the chi-squared test, Fisher’s exact probability test, Wilcoxon rank-sum test, Cochran–Mantel–Haenszel chi-square test, and weighted least squares covariance. Quantitative data will be described using the mean, standard deviation, median, quartile thresholds, and minimum and maximum values of the range. The *t*-test will be used for comparative analysis of data showing normal distribution; it will be used with Satterthwaite correction if the variance is uneven. Quantitative data exhibiting non-normal distribution on the Wilcoxon rank-sum test will be analyzed using the Wilcoxon signed-rank sum test and covariance generalized linear models. The main analyses include an intention-to-treat (ITT) analysis and a per-protocol subject analysis of the primary outcomes. The ITT analyses will include all randomized patients. The last observation carried forward method will be used in the ITT analysis for missing data imputation. Subgroup analyses will be performed based on the severity of the disease. All hypothesis tests will be two-sided. The test statistics and corresponding *P*-values will be reported. Statistical significance will be established at *P*< 0.05, with a high statistical significance established at *P*< 0.01.

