#### Primary outcome

The primary outcome is analgesic effectiveness, assessed as pain in the worst affected joint, which will be measured using the visual analog scale at rest and with activity. The patients will be evaluated from baseline to 5 days post-randomization (4 h, day 1, day 2, day 3, day 4, and day 5) and during the follow-up period. The primary efficacy endpoint will be the assessment of joint pain on treatment days 2–5.

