### Sample size

The required sample size was calculated using an estimation formula based on the differences among the three sample rates [14, 17, 18]. A previous clinical study [19] reported that the response rates of the etoricoxib treatment, TCM treatment group, and placebo treatment groups were 63.89%, 42.5%, and 15.5%, respectively. Setting the two-sided significance level (*α*) at 0.05 and statistical power at 0.8, a minimum sample size of 74 participants per group (222 participants in total) was estimated to provide sufficient statistical power to detect a between-group difference of approximately 20% in treatment efficiency, defined as the change in analgesic effectiveness. Considering a 20% loss to follow-up, we aim to enroll 89 patients in each arm, that is, a total of 267 patients.

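### LOCF in the ITT analysis assumes pain stays flat after withdrawal, which the protocol's own account of a self-limiting attack contradicts within the day 2–5 endpoint window

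*Protocol article*

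**What the plan says.** The Statistical analysis section of the protocol article plans two populations: "The main analyses include an intention-to-treat (ITT) analysis and a per-protocol subject analysis of the primary outcomes". The ITT set is everyone randomized, and its missing values are handled by one stated method: "The last observation carried forward method will be used in the ITT analysis for missing data imputation". The per-protocol analysis is a second population; it does not fill in missing scores.

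Three other places bear on that choice.

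- Treatment cycles describes the natural course: "The pain associated with acute GA is self-limiting; that is, it can resolve on its own after approximately 1 week without medication". It then tells patients that "if they cannot bear the pain, they can withdraw from the study at any time and choose other treatment options".
- Primary outcome fixes the window: "The primary efficacy endpoint will be the assessment of joint pain on treatment days 2–5". It lists VAS scores at 4 h and on each of days 1 to 5.
- Sample size makes one allowance for loss, the same in every arm: "Considering a 20% loss to follow-up, we aim to enroll 89 patients in each arm".

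Termination and withdrawal adds that investigators will try to obtain a final evaluation from patients who leave. It does not say how that evaluation enters the ITT analysis.

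**The concern.** LOCF is right for a patient whose pain would have stayed at its last recorded level. The protocol says the opposite about this disease, and the endpoint window lies inside the expected decline. The last score before a pain-driven withdrawal is also likely to be high by selection. For both reasons carried-forward scores tend to overstate later pain relative to the natural course.

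Whether this matters for the comparison depends on how the overstatement is spread over the arms. One arm receives double placebo, and the planning figures differ widely: "response rates of the etoricoxib treatment, TCM treatment group, and placebo treatment groups were 63.89%, 42.5%, and 15.5%, respectively". On those figures, equal pain-driven withdrawal in all three arms cannot be taken for granted. If placebo patients leave more often, their frozen scores add to the apparent benefit of HZG. If HZG patients leave more often than etoricoxib patients, HZG is penalised. Either way, part of the estimated difference would come from when patients left and not from the drug.

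**Working it through.** **The plan's own figures.** The 74 per group reproduces as 15.5% versus 35.5% (placebo plus 20 points), two-sided 0.05, power 0.80, pooled variance, no continuity correction. The 89 is 74 × 1.2 = 88.8, rounded up. Nothing below changes these figures. They supply the 20% loss and the 89 per arm used here.

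**One patient.** Let pain fall by s mm per day. For a patient last seen on day 2, the carried score exceeds the expected score on days 2, 3, 4 and 5 by 0, s, 2s and 3s.

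- Day 2–5 mean: (0 + 1 + 2 + 3)s / 4 = 1.5s.
- Day 5 alone: 3s.
- The documents give no s. At 5, 9 and 10 mm/day the excess on the mean is 7.5, 13.5 and 15 mm.

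**The arm contrast.** For placebo minus HZG, bias = d_P × g_P − d_H × g_H. Here d is the share withdrawing in an arm and g is the mean excess of carried over expected pain in those who withdraw.

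**No drug effect.** Assume s = 9 and withdrawal unrelated to pain, spread evenly over last visits on days 1, 2 and 3. The excess on the day 2–5 mean is 2.5s, 1.5s and 0.75s respectively, so g = (2.5 + 1.5 + 0.75)/3 × 9 = 14.25 mm in both arms.

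| Dropout, placebo vs HZG | Bias by formula | Range when pain-driven withdrawal is also simulated |
|---|---|---|
| 20% vs 20% | 0 | about 0 |
| 20% vs 15% | 0.05 × 14.25 = 0.7 mm | 0.7–1.0 mm |
| 20% vs 5% | 0.15 × 14.25 = 2.1 mm | 2–3 mm |

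The simulations used 89 per arm and a 70 mm baseline. At 20% versus 15% the rejection rate stayed at about 3–7%. At 20% versus 5% it was about 10–21%, and 8.5–27% over a wider set of assumptions (between-patient SD 8–20 mm, residual SD 8–12 mm). The documents give no SD, so no single type I error can be quoted.

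**A real effect.** Assume falls of 10 mm/day on active and 7 on placebo, withdrawal after day 1 or day 2, and day 5 as the contrast. The mean excess is 3.5s. The simulated true difference was 14.2 mm.

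- 20% in both arms: 0.2 × 3.5 × (7 − 10) = −2.1, giving 12.1 mm. The benefit shrinks although dropout is equal, because the rates of decline differ.
- 10% active, 30% placebo: 0.3 × 3.5 × 7 − 0.1 × 3.5 × 10 = 3.85, giving 18.05 mm (18.2 simulated). The benefit grows.

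**Responder scale.** Take 42.5% versus 15.5%, a difference of 27.0 points, and assume early leavers count as non-responders but would otherwise have responded at their arm's rate.

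- 20/20 dropout (HZG/placebo): 34.0 − 12.4 = 21.6 points.
- 10/30: 38.25 − 10.85 = 27.4 points.
- 30/10: 29.75 − 13.95 = 15.8 points.
- No true effect (15.5% in both arms), 10/30: 13.95 − 10.85 = 3.1 points.

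**The visit schedule.** Table 2 marks VAS at allocation, day 5, end of intervention and week 1, with nothing on days 1 to 4. If that schedule were followed, LOCF would carry the baseline score to day 5, an excess of 5s, or 45 mm at 9 mm/day.

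**The case against.** The strongest reply is that size and direction rest on dropout by arm, which the protocol does not give. It has one 20% allowance for all arms. That allowance covers loss to follow-up in a study with a week-1 visit, so some of it may fall after day 5. This stands. A reader might infer that LOCF necessarily biases the contrast, or necessarily favours HZG. The documents support neither: with no drug effect and equal dropout the mean bias is zero, and with modest imbalance it is below or about 1 mm.

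The trial is sized on response rates, and counting a patient who leaves in unbearable pain as a non-responder is a defensible composite choice that LOCF partly mimics. This also stands, but the primary endpoint is worded as joint pain on days 2–5, and no responder rule is stated. If a composite is intended, it should be named rather than produced as a by-product of imputation.

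MMRM is not a complete cure. It assumes missing at random, which fails if withdrawal depends on pain that was never recorded. That is a reason for one targeted sensitivity analysis, not for keeping LOCF.

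The statistical analysis plan is not shown and may contain sensitivity analyses. Their absence from the article is therefore no fault. LOCF is a different matter, because the article states it as the method.

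Finally, a reader might take unbearable pain to be the only way out of the study. The protocol also allows withdrawal for side effects, organic disease, clinical indication, combined drugs or any reason. The argument needs only that pain is one stated route.

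**Conclusion.** The concern holds as a criticism of a stated choice. LOCF's flat-pain assumption conflicts with the protocol's own description of the attack, inside the primary window, and a stated reason for leaving is tied to the outcome. For those who leave, carried scores overstate later pain relative to the natural course.

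The effect on the comparison is conditional. It arises when withdrawal or rate of decline differs between arms, and its sign follows the arm that loses more. Under the assumptions shown, it is about 0.7–1 mm at 20% versus 15% and 2–3 mm at 20% versus 5%. Type I error is clearly above nominal only under strong imbalance, by an amount that depends on the assumed SD.

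Standard errors are unreliable as a measure of precision even with equal dropout, because carried values count as measurements. A reader might infer that the test then has the wrong level too. That does not follow: if the arms are identical in course and in withdrawal, a two-sample comparison of the filled-in data still compares like with like.

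**What to change.** 1. In Statistical analysis, replace LOCF as the primary ITT method with a likelihood-based repeated-measures model (MMRM) on the VAS scores listed under Primary outcome. Include arm, day, arm-by-day and baseline VAS, and give the day 2–5 contrast from the model. Include any evaluation obtained after withdrawal under Termination and withdrawal, and say so.
2. Keep LOCF at most as a sensitivity analysis.
3. Unless the statistical analysis plan already has one, add a single sensitivity analysis for pain-related withdrawals, for example placebo-based multiple imputation. State the estimand it targets, since counting leavers as failures or imputing them from placebo answers a different question from the MMRM.
4. Reconcile Table 2 with Primary outcome. The model needs the day 1 to 4 scores that Table 2 does not mark.

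The cost is new analysis wording and some extra programming, and the primary result will rest on a missing-at-random assumption. No extra patients are needed. Daily VAS after withdrawal is not required; it would go beyond the final evaluation the protocol foresees. The change should be fixed before unblinding.

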### Adverse events

The Chinese herbal medicines contained in HZG are listed in the Pharmacopeia of the People’s Republic of China. The dose proposed for use in this study is within the range recommended by the Pharmacopeia Commission of the Ministry of Health of the People’s Republic of China. To date, no adverse reactions have been reported in relation to the clinical application of HZG.

Blood and urine samples, liver function, renal function, and electrocardiograms will be examined before the start of treatment and after 5 days of treatment. Researchers will focus on identifying any abnormal changes in the results. All AEs will be collected and graded by the assessor at each visit to determine the severity and potential relationship to treatment. The safety assessment includes the incidence of treatment-induced or serious adverse events, withdrawals due to adverse events, and changes in laboratory parameters. All drugs in this trial will be immediately discontinued in the event of a serious adverse event. The specific implementation of such measures is presented in Table 2. In addition, all severe AEs will be reported to the first responsible staff member and to the ethics committee within 24 h.

**Table 2 Tab2:** Schedule for enrollment, intervention, and assessment

	Phase	Screening/enrolment	Allocation	Treatment/intervention					End of intervention	Follow-up
Activity	Time points	Day 0		Day 1	Day 2	Day 3	Day 4	Day 5		Week 1
**Screening/enrolment**	**Eligibility screening**	X	X							
	**Obtaining informed consent**	X								
	**Clinicopathological evaluation**	X								
	**Medical history taking**	X								
	**Enrolment**	X								
	**Random allocation**		X							
	**Biological specimen collection**		X						X	X
**Treatment/intervention**	**HZG+ placebo etoricoxib**			**★----------------------------------------------------★**						
	**Etoricoxib + placebo granules**			**☆----------------------------------------------------☆**						
	**Placebo granules + placebo Etoricoxib**			**○----------------------------------------------------○**						
**Outcome assessment**	**VAS score**		X					X	X	X
	**Tenderness, redness, and swelling of the involved joint**		X					X	X	X
	**Symptom relief time**		X					X	X	X
	**Patient satisfaction**		X					X	X	X
	**36-Item Short Form Survey**		X					X	X	X
	**CRP**		X					X	X	
	**IL-1**		X					X	X	
	**IL-6**		X					X	X	
	**IL-8**		X					X	X	
**Safety assessment**	**Vital signs**		X					X	X	
	**BR**		X					X	X	
	**BB**		X					X	X	
	**RUT**		X					X	X	
	**DC**		X					X	X	
	**ECG**		X					X		
	**PE**		X					X	X	
	**AEs**		X	X	X	X	X	X	X	
	**Severe AEs**		X	X	X	X	X	X	X	

*✩****○*** intervention in the control group, *★* intervention in the experimental group, *HZG Huzhang* granules, *VAS* Visual analog scale, *CRP* C-reactive protein, *IL* Interleukin, *BR* Blood routine, *BB* Blood biochemistry, *RUT* Routine urine test, *DC* Drug combination, *ECG* Electrocardiogram, *PE* Physical examination, *AE* Adverse event

### Termination and withdrawal

The trial will be terminated for any participant who develops one or two of the following conditions during the trial: (1) intolerable side effects and (2) serious acute or chronic organic disease. Any participant can withdraw from the trial at any time and for any reason without affecting the current or future treatment. Investigators will attempt to contact any participant who withdraws or discontinues to complete the final evaluation. The reasons for withdrawal or termination and the time of the last dose will be recorded. All withdrawals and terminations will be reported and analyzed.

### Data management and monitoring

All physicians, assessors, and research assistants will attend training workshops before the trial. Data entry will be completed using the case management system specifically designed for this trial by Jiangsu Famaisheng Medical Technology. Data collection will include all the information in the case report forms. The data will be entered using the double-entry method. To ensure the quality and consistency of the source data and of the data entered into the database, two researchers will independently check the source data and compare them against the information entered into the corresponding electronic case report forms. Any questions or suspicions arising during the process of checking the source and case report data shall be added to a formal list of queries, which will be addressed by the investigator filling out the data. If a problem is found, it will be processed and recorded in a timely manner. All documentation on quality control will be maintained to objectively assess the safety and key outcomes. The quality control personnel of the Shanghai Yueyang Integrated Hospital (Shanghai, China) will regularly monitor the data collected during the entire study period. The data monitoring committee will assess the safety data and critical efficacy outcomes after the trial is completed. Jiangsu Famaisheng Medical Technology, which is independent of the sponsor and investigators, will perform data audits in the middle of the trial. Interim auditing will include off-site surveillance and submission of a report on the progress of the study. All possible efforts will be made to maintain confidentiality of patient data by using multiple means, such as de-identification, use of password-protected secure servers, and restriction of access to study team members.

## Discussion

GA is caused by the deposition of MSU crystals in soft tissue, triggering severe but self-limited bouts of acute arthritis accompanied by intense pain, as well as articular and periarticular inflammation [19]. The acute attack of gout not only causes joint pain and dyskinesia, but more importantly, gout is associated with a number of complications, including hypertension, chronic kidney disease, cardiovascular disease, obesity, insulin resistance, diabetes, and hyperlipidemia [20–22].

In the early stages, gout often manifests as intermittent acute arthritis. A single joint is mainly involved, most commonly the first metatarsophalangeal joint. Joint swelling and pain usually last for 7 days, can be spontaneous or relieved by drugs, and do not have any symptoms during the interval [22]. With the extension of the course of gout, the number of attacks and the number of joints involved gradually increase, and joint symptoms begin to appear during the interval [23]. At the same time, the tophus is formed in the joint, skin, and soft tissue, and the joint is damaged or even maimed. Although gout treatment is effective, the compliance of patients with gout is unsatisfactory [24]. Poor compliance not only directly affects the therapeutic effect on patients but also places a heavy burden on the entire medical and health department [25–28].

TCM has been used for the treatment of gout for a long time, and its curative effect is remarkable. TCM considers that GA is caused by internal and external causes; the external causes mainly include wind, cold, dampness, and heat, while the internal causes mainly include the deficiency of vital *qi* of the human body, disorder of ascending clear and descending turbid function of spleen and kidney, and deficiency of *qi* and blood, leading to dampness-heat, turbid phlegm, stagnation of blood stasis, spleen deficiency, and other syndromes [29, 30], among which dampness-heat syndrome is the most common cause. Based on clinical practice, combined with the TCM-based pathogenesis of GA, our research group has formulated the TCM prescription of HZG, which is used to treat GA on the basis of the treatment principles of clearing heat, removing dampness, and dredging collaterals.

Previous research indicated that HZG has an anti-inflammatory effect on the downregulation of NALP3 and caspase-1 at the protein translation level [31]. Based on these previous observations, we cultured fibroblast-like synoviocytes stimulated by MSU with serum containing HZG and found that HZG inhibited the expression of IL-1β, TNF-α, and IL-6 [14]; this supports the therapeutic effect of HZG in patients with GA showing dampness-heat syndrome and motivated us to initiate this trial.

In this trial, we will use the granule formulation to minimize deviations associated with the use of herbs from different geographical regions, different varieties, and maintained under different storage conditions. We chose etoricoxib as a comparative drug. Etoricoxib is a new cyclooxygenase-2 (COX-2) inhibitor that can be used in the treatment of GA. The 2012 American College of Rheumatology guidelines for the management of gout indicate that etoricoxib has an evidence-based grade of A in the treatment of GA when using COX-2 inhibitors [32]. In this study, we aimed to clarify the efficacy of HZG treatment twice daily for 5 days. As acute GA is prone to recurrence, we emphasize a 1-week follow-up after the end of treatment.

We will carefully monitor the recurrence after the end of GA treatment. In addition, we will record all AEs and information regarding concomitant medications at each visit. The study results will help clarify the efficacy of HZG, as well as its safety in the treatment of GA in terms of both inflammation regression and rate of recurrence. We expect that this study will provide high-quality evidence that can be used to develop clinical treatment guidelines. Therefore, the results of this study are expected to have an important impact on public health.

The limitations of the study should be mentioned. Only one trial drug regimen will be tested, and the prescription will not be adjusted according to symptoms, which means that the results may be specific to the test regimen. In addition, because of the reliance on etoricoxib as the control drug in our study, our findings may not apply to the adverse reactions of other NSAIDs. Nevertheless, the findings will still be useful as a reference in clinical practice and will help pave the way for future research. Finally, the HZG prescription to be used in this trial was designed for the treatment of GA with dampness-heat syndrome; thus, the findings may not be applicable to other syndromes.

